### Recruitment

The main participants in this trial will be recruited simultaneously through the outpatient and inpatient systems of the three centers, and we will also recruit online through websites and hospital-based WeChat ads of the three centers. Posters, pictures, and videos related to the study will be produced to help participants understand the purpose of this study, while explaining the advantages and disadvantages of the treatment and what they need to do to participate in this study. Based on the inclusion/exclusion criteria, we will make a preliminary judgment and screening of the possibility of inclusion of participants who are interested in participating in the study, and determine whether the subject is included according to the results of the examination. Participants who meet the inclusion criteria will be informed of the study details, and subjects or their legal guardians will be required to sign an informed consent form before treatment begins. The recruitment of participants began on 1 December 2019 and is expected to end in June 2021, or it may be completed early if a sufficient number of patients are recruited.

### Randomization

All included patients will be randomly divided into two groups at a ratio of 1:1: the EA plus NR group and the EA group. A specialized statistician who is not a researcher in this study will be entrusted to use randomization software to generate random-number sequences for randomization. Meanwhile, the allocation should be hidden. Strips identifying participants by grouping information will be hidden in sealed opaque envelopes with sequential numbers. The envelopes will not be opened until informed consent is obtained. Each clinical research center will select cases strictly according to the inclusion and exclusion criteria, will determine the eligible patients who can be included, and then will obtain random numbers and grouping information by phone until the total number of patients (206) is reached.

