### Sample size

We will conduct this study using a randomized controlled trial design, and the main observed outcome will be improvements in patient cognitive function. Our previous small-sample (20 cases) clinical observation found that 2 weeks of EA plus routine cognitive rehabilitation treatment and EA plus NR and routine cognitive rehabilitation treatment can reduce scores on the MOCA scale by 3.17 ± 2.12 and 4.40 ± 2.59 points, respectively. With the significance test level set at 0.05 and the test power at 0.9, the sample size was calculated by using the following:
$$ N=2\times {\left[\left({z}_{\alpha /2}+{z}_{\beta}\right)\times \upsigma /\updelta \right]}^2 $$

*N* is the required sample size for each group, and the sample size of each group is equal. When *α* is 0.05 and *β* is 0.1, the normal distribution quantile table shows the following:
$$ {Z}_{\alpha /2}=1.96 $$

and
$$ {Z}_{\beta }=1.282. $$

*σ* and *δ* represent the larger standard deviation and the mean difference between two groups, which are 2.59 and 1.23, respectively. By substituting the above data into the formula, it was calculated that 93 patients will be needed in each group. Accounting for a 10% dropout rate, the final estimated sample size is approximately 103 patients in each group (206 in total).

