### Statistical analysis

Statistical analysis of all data will be performed using SPSS 22.0 software by specialized statisticians who are not the principal researchers. Classified variables will be analyzed using Pearson’s *χ*^2^ test or Fisher’s exact test, and continuous variables will be evaluated using Student’s *t* test or an appropriate nonparametric method. The measurement data from different treatment groups will be statistically described by the mean ± standard deviation. When comparing within groups or between groups, a normality test and homogeneity of variance test will be performed before data analysis of each group. If the data satisfy the normal distribution and homogeneity of variance, then the *t* test will be used for comparison between two groups, and the LSD or SNK method will be used for multiple comparisons. Conversely, the rank-sum test will be used for nonnormality or nonuniformity of variance. The significance level used for statistical analysis with 2-tailed testing will be set at 5%.

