## Discussion

The effective improvement of cognitive impairment after stroke is particularly important to improve the rehabilitation and quality of life of patients after stroke, so it is necessary to take effective treatment measures to improve cognitive function. Acupuncture therapy has a history of more than 2000 years in China and has been widely used in Western countries in recent years. Our previous clinical research found that EA treatment at Baihui (GV20) and Shenting (GV24) along with NR on the head can effectively relieve cognitive impairment after stroke. However, the best acupuncture treatment mode and the cumulative effects of acupuncture still need further research and confirmation. Therefore, we propose a prospective, multicenter, large-sample randomized controlled trial to explore the cumulative effect of acupuncture and needle retention. This study is expected to provide a preliminary basis for the optimization of treatment methods for PSCI, to further develop a standardized, simple, effective, and easy-to-promote comprehensive TCM clinical rehabilitation treatment method.

Although most of the previous studies on acupuncture treatment of cognitive impairment used a combination of body acupuncture points and head acupoints [23–25], we will use only two acupuncture points on the head (GV20 and GV24) for treatment, which is based on the results of literature analysis and a continuation of previous research [26, 27]. In addition, unified acupuncture points may reduce variability and increase the accuracy and persuasiveness of this study. In recent years, the MMSE, MOCA, and BI scales have been used to assess various aspects of cognitive function, so we used these three items as outcome indicators to reduce the interference of subjective factors and simplify the assessment of cognitive impairment. In addition, the multicenter design of the study may introduce a bias, mainly by including differences between acupuncture operator techniques. Therefore, to eliminate the bias caused by operator inconsistency, we will conduct unified training for all the acupuncturists participating in this study and strictly regulate the acupuncture operation to maximize the elimination of this bias. However, although all results will be measured and recorded by independent researchers to minimize the risk of detection bias, as a limitation of this protocol, we cannot use double-blind procedures to conduct this study due to the nature of acupuncture treatment.

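### The plan names differences between operators across centres as a bias, but its stated comparison leaves centre out; the cost is precision, not validity

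*Protocol article*

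**What the plan says.** All references are to the protocol article.

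- **Discussion.** The authors state that "the multicenter design of the study may introduce a bias, mainly by including differences between acupuncture operator techniques". Their answer is common training of the acupuncturists and tight regulation of the procedure.
- **Study setting.** Patients are treated in the hospital that recruited them, so operators are nested in centres. Trial design names three centres, all in one city.
- **Randomization.** Allocation is 1:1 from computer-generated sequences held by an independent statistician. Each centre "will obtain random numbers and grouping information by phone until the total number of patients (206) is reached". No stratification by centre is described.
- **Statistical analysis.** For continuous outcomes, if normality and equal variance hold, the t "test will be used for comparison between two groups"; otherwise a rank-sum test is used. Neither is described with a centre term.
- **Sample size.** The planning inputs σ and δ "represent the larger standard deviation and the mean difference between two groups, which are 2.59 and 1.23, respectively", and "it was calculated that 93 patients will be needed in each group". The formula has no centre component.

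**The concern.** The plan identifies a source of variation tied to centre and then fixes a comparison that ignores it. This is not merely a detail left to a later document, because the section on statistical analysis names the test. Centre is known for every patient, so the omission is avoidable.

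Two things are at stake. If allocation does not balance arms within centres, any single trial can have more patients of one arm in a better-performing centre, and that difference stays in the estimate. Variation between centres also stays in the error term, so the comparison is less precise than the same data allow.

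**Working it through.** **Inputs from the document.** Two-sided α 0.05, power 0.90, σ = 2.59, δ = 1.23 MOCA points, 93 per arm before dropout, 10% dropout, 103 per arm, three centres.

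**Input not in the document.** The between-centre share of outcome variance (ICC). I assume 0.01 to 0.20 and three equal centres.

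**1. Reproduce the plan's figure.** N = 2[(1.96 + 1.282) × 2.59 / 1.23]² = 93.2, stated as 93. Then 93 / 0.90 = 103.3, stated as 103 per arm and 206 in total. The figures reproduce, apart from rounding down. Power at 93 per arm is Φ(1.23 / (2.59 × √(2/93)) − 1.96) = Φ(3.238 − 1.96) = 0.899.

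**2. Power with and without centre.** The document does not say whether 2.59 contains centre variation, so both readings are shown.

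- Reading A, 2.59 is within-centre: the unadjusted test works with SD 2.59 / √(1 − ICC). A centre term keeps power near 0.90.
- Reading B, 2.59 is the total SD: the unadjusted test keeps 0.899. A centre term works with SD 2.59 × √(1 − ICC).

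| ICC (assumed) | A: SD, unadjusted | A: power, unadjusted | A: n per arm for 90% | B: power, unadjusted | B: power with centre |
|---|---|---|---|---|---|
| 0.01 | 2.603 | 0.897 | 95 | 0.899 | 0.902 |
| 0.05 | 2.657 | 0.884 | 99 | 0.899 | 0.914 |
| 0.10 | 2.730 | 0.867 | 104 | 0.899 | 0.927 |
| 0.20 | 2.896 | 0.826 | 117 | 0.899 | 0.952 |

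Example, reading A at ICC 0.10: Φ(1.23 / (2.730 × √(2/93)) − 1.96) = Φ(1.112) = 0.867.

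**3. Validity and chance shift.** I simulated 10,000 trials per setting with 186 patients analysed, 93 per arm, three equal centres and total SD 2.59. The shift is the part of the treatment contrast due only to unequal centre mix between arms.

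| ICC (assumed) | Unstratified: type I error, unadjusted | Unstratified: 95th percentile of shift size (share of δ) | Stratified: type I error, unadjusted | Stratified: type I error with centre |
|---|---|---|---|---|
| 0.05 | 0.051 | 0.17 points (14%) | 0.043 | 0.049 |
| 0.10 | 0.052 | 0.24 points (19%) | 0.039 | 0.051 |
| 0.20 | 0.050 | 0.34 points (27%) | 0.027 | 0.048 |

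The mean shift under unstratified allocation is zero to within simulation error. Under stratified allocation the shift is zero in every trial, but the unadjusted test still counts centre variance as error and so rejects too rarely.

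**The case against.** The strongest case against the point has four parts.

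- **The allocation method is not stated.** A reader might infer that all three hospitals draw from one unstratified list by simple randomisation, and then compute how often arms or centres would be unbalanced. The text does not support that. Randomization speaks of sequences and Implementation of a sequence, and neither says simple, unblocked or single-list. Recruiting to a total of 206 is equally compatible with separate blocked lists per centre. The article condenses a fuller protocol, where such detail commonly sits. This objection stands, and nothing here rests on that inference.
- **Randomisation already protects validity.** A reader might also conclude that centre biases the treatment contrast. It does not: imbalance has mean zero and type I error stays near 5%. This stands too.
- **The centre variance may be small.** The planning quantity is change in MOCA, so stable differences in level between centres largely cancel. The hospitals share a city and the operators share training. ICC 0.20 under reading A means a between-centre SD of 2.59 × √(0.20/0.80) = 1.30 points, more than the 1.23-point treatment difference. The upper end of the range is therefore demanding. The plan also has slack, because it uses the larger pilot SD. With the pooled value √((2.12² + 2.59²)/2) = 2.37, power at 93 per arm is 0.943. These points limit the size of the concern but do not remove it.
- **Centre is not operator.** The named bias concerns technique, and a centre term cannot remove differences between operators in the same hospital. This stands as a limit of the fix.

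The stated test remains. Whichever way allocation is done, leaving centre out gives no benefit beyond 2 degrees of freedom.

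**Conclusion.** The point holds as a modest loss of efficiency. The plan acknowledges a difference linked to centre, relies on training to remove it, and states a comparison that cannot account for what remains.

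- **If allocation is unstratified:** the test is valid and the estimate is unbiased on average. Under reading A, power falls short of the planned 0.899 by about 3 points or less for ICC up to 0.10 and by about 7 points at 0.20. Under reading B, the plan forgoes a gain of about 0 to 5 points. The chance shift in the estimate reaches 0.17 to 0.34 points at its 95th percentile for ICC 0.05 to 0.20.
- **If allocation is stratified by centre:** the unadjusted test is conservative and wastes the benefit of stratifying.

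These sizes rest on an assumed ICC and equal centres, since the document gives neither. The evidence does not support calling the contrast biased, nor changing the randomisation lists during recruitment.

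**What to change.** In Statistical analysis, replace the unadjusted t or rank-sum comparison with a linear model containing treatment and centre as fixed effects, for MMSE, MOCA and the Barthel Index. Report the treatment effect by centre descriptively, without separate significance claims. State in Randomization whether the sequence is stratified by centre.

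The cost is 2 degrees of freedom out of about 184, a variable already on record for every patient, and a short amendment. Quality control routes plan changes through the ethics committee, so the amendment should be made before the data are analysed. No change to the randomisation lists is needed. The text should also say that a centre term leaves operator differences within a hospital untouched, so training remains the only safeguard there.

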### Implementation

A specialized statistician who is not a researcher in this study will generate the allocation sequence. Relevant independent researchers in each center will enroll participants and assign participants to different interventions.

### Blinding

Due to the limitations of this protocol and the nature of acupuncture treatment, we were unable to adopt a double-blind study design. To improve the quality of this study as much as possible, an outcome-assessor-blinded trial procedure will be implemented. With the exception of the evaluation process, the evaluator will not contact any participants. In addition, to prevent nonblind participants or researchers from biasing the outcomes, this study will only involve individuals with no conflicts of interest or preconceived positions. In the process of data management and statistical analysis, we will invite independent professionals to handle data management, and the statistical analysis of all data will be performed by professional statisticians who are not the principal researchers.

### Intervention

Participants in the two groups will receive different treatments 5 times a week for 8 weeks in separate compartments. All acupuncturists will be physicians with at least 3 years of experience in acupuncture practice. Meanwhile, each participant will receive the same routine cognitive rehabilitation treatments from therapists who will be blinded to the treatment allocation. The interventions in the two groups are as follows:

#### EA plus NR group

In addition to routine cognitive rehabilitation treatments, participants in this group will receive EA treatment. The regular acupuncture method will be applied at Baihui (GV20) and Shenting (GV24). With the patient in the supine position, a 75% alcohol cotton swab will be used to routinely disinfect the two acupuncture points, and Huaying stainless steel acupuncture needles (0.25 mm × 25 mm) will be used, keeping the angle between the needle tip and the scalp at 30°, and the needle tip will be moved backwards along the anterior-posterior midline, and the needle will be inserted 0.5 cun. After insertion, manipulations will be applied for the “Deqi” sensation. The EA therapeutic apparatus (G6805-2A, Shanghai Huayi Medical Instrument Co., Ltd., China) will be connected to the needles at the two acupuncture points with 15 min of continuous waves and 15 min of dense waves at a frequency of 2.5 HZ. After a total of 30 min of stimulation, the EA therapeutic apparatus will be removed. Then, the needles will remain at the acupuncture points for 1 h, and manipulations will be performed every 30 min until the needles are removed.

#### EA group

In addition to routine cognitive rehabilitation treatments, the intervention of this group will be the same as that in the EA plus NR group except that the needles will be directly removed after 30 min of electrical stimulation. There will be no NR process.

#### Routine cognitive rehabilitation treatments

According to the actual situation of all participants in the two groups, we will follow the theory of neuropsychology and provide each participant with the same cognitive rehabilitation treatment through a combination of artificial training and computer training that will include classification exercises, rule (response) suppression exercises, plan analysis exercises, reasoning comprehension exercises, working memory exercises, and comprehensive ability exercises.

### Outcome measures

All participants will be evaluated at these time points: baseline, week 4, week 8, and follow-up week 12 and week 24 after all treatments are completed. All treatment evaluations will be conducted by researchers who will be blinded to the treatment allocation.

#### Primary outcomes

##### Mini-mental state examination (MMSE)

The MMSE scale is the most widely used cognitive function assessment questionnaire and has the advantages of simplicity, time savings, convenient operation, and relevance for a wide range of people [20]. It consists of 30 questions including orientation, memory, calculation, recall, and language. Each answer is worth 1 point for a total of 30 points. The assessment criteria for cognitive impairment vary with the patient’s educational level: illiterate or semi-illiterate ≤ 17 points, primary school ≤ 20 points, and middle school ≤ 24 points. The lower the MMSE scale score is, the worse the cognitive function is considered.

##### Montreal cognitive assessment scale (MOCA)

The MOCA is currently one of the generally acknowledged cognitive impairment screening scales [21], which mainly includes items such as attention and concentration, executive function, memory, speech, visual structure, abstract thinking, computing power, and orientation. Compared with the MMSE, the MOCA has better sensitivity and specificity for patients with mild cognitive impairment. The total possible score is 30 points. If the subject has been educated for 12 years or less, 1 point is added, and a score of < 26 points is considered to indicate cognitive impairment.

#### Secondary outcome

##### Barthel Index (BI)

BI is a questionnaire for assessing activities daily living [22]. It mainly includes the ability to control urination, eating, wearing, walking, bathing, and other daily life activities. Each item has a score of 0, 5, 10, or 15 points based on the degree of disruption, and the total possible score is 100 points. A higher score indicates a worse living ability. BI classification is as follows: heavy dependence (score 0–40), moderate dependence (41–60), light dependence (61–99), and without dependence (100).

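### The Barthel Index direction is stated backwards: the sentence says higher is worse, but the bands beside it make higher better (with a smaller wording slip on MOCA in the sample size)

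*Protocol article*

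**What the plan says.** **Barthel Index.** The Secondary outcome section of the protocol article names the BI as its single measure, with a maximum of 100 points. On direction it says: "A higher score indicates a worse living ability". The classification that follows is: "heavy dependence (score 0–40), moderate dependence (41–60), light dependence (61–99), and without dependence (100". Activities of daily living, which the BI measures, also appear in the first trial objective.

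**MOCA.** The Sample size section opens by saying that "the main observed outcome will be improvements in patient cognitive function". It then reports that in a 20-case pilot, EA and EA plus NR (each with routine cognitive rehabilitation) "can reduce scores on the MOCA scale by 3.17 ± 2.12 and 4.40 ± 2.59 points, respectively". The MOCA section gives a maximum of 30 and states that "a score of < 26 points is considered to indicate cognitive impairment".

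**MMSE, for comparison.** The MMSE section gives the direction correctly: a lower score means worse cognition.

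**The concern.** The direction sentence and the bands for the BI cannot both be true. The sentence is the one place where the article says outright which end of the scale is good, and it names the wrong end. The preceding description of item scoring does not help, because it ties points to how far function is disrupted without saying which end earns more.

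This matters for interpretation. The Blinding and Statistical analysis sections give the analysis to statisticians who are not the principal researchers, and the planned tests are two-tailed. A two-tailed p-value says that the arms differ. Which arm did better comes from the sign of the difference read against the scale's stated direction. With the stated direction reversed, the conclusion on daily living would be reversed too.

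The MOCA wording is a lesser matter of the same kind. A fall on a scale where low scores mean impairment is a decline, yet the sentence is offered as evidence that the treatments help.

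**Working it through.** **1. BI: the sentence against the bands**

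| BI score | Band in the protocol article | Direction implied |
|---|---|---|
| 0–40 | heavy dependence | worst |
| 41–60 | moderate dependence | better |
| 61–99 | light dependence | better still |
| 100 | no dependence | best |

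Dependence falls at every step as the score rises, so higher is better. The sentence says higher is worse.

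Illustration (the article gives no expected BI change, so these values are chosen only to show the sign): a patient goes from 40 to 100, a change of 100 − 40 = +60. By the sentence, this is 60 points worse. By the bands, it is a move from heavy dependence to none.

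For the group comparison, let D = mean BI (EA plus NR) − mean BI (EA). The estimate D does not depend on the direction label, and a two-sided p-value depends only on the size of the test statistic. Only the reading changes: D > 0 means EA plus NR did worse by the sentence and better by the bands.

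**2. MOCA: the pilot sentence against the cut-off**

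Inputs from the Sample size section: changes of 3.17 (SD 2.12) with EA and 4.40 (SD 2.59) with EA plus NR; σ = 2.59, δ = 1.23, z values 1.96 and 1.282, dropout 10%.

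- As worded: −3.17 and −4.40, so both arms decline on a scale where a score under 26 marks impairment.
- Read as improvement: +3.17 and +4.40, so both arms gain.
- In either case the size of the difference is 4.40 − 3.17 = 1.23.

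The second reading fits the section's own opening statement. It also fits the Discussion, which says that earlier work found EA with NR to relieve cognitive impairment after stroke.

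**3. Does the sample size depend on it?**

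The plan's own figure first:

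- N = 2 × [(1.96 + 1.282) × 2.59 / 1.23]² = 93.2 per group; the plan states 93.
- 93 / (1 − 0.10) = 103.3 per group; the plan states about 103, or 206 in total.

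With δ = −1.23 in place of +1.23, the squared term is the same and N is again 93.2. Power at 93 per group is 0.899 with either sign. The BI does not enter the calculation.

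**The case against.** The best reply is that nothing computed in this trial uses either faulty sentence. The Statistical analysis section plans two-tailed t tests or rank-sum tests; no one-sided test is stated. Group means, differences and p-values are the same whichever way the sentence reads, and the bands beside it show the right direction. To misreport the BI, someone would have to use the sentence and ignore the bands. All of this stands, and it limits the consequence to interpretation. It does not remove the contradiction: the explicit rule for the only secondary outcome is still wrong as written.

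On MOCA, the reply is that the fault is a verb describing past data and not a scoring rule. That also stands, which is why this part is secondary.

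A reader might infer more than the article supports:

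- **That the planning hypothesis has the wrong sign, or that the trial was planned on harm from EA plus NR.** The article states no signed hypothesis. δ is given only as the mean difference between the groups, an unsigned 1.23 that enters squared.
- **That the sample size is wrong because of the verb.** The stated figures reproduce and do not move when the sign changes.
- **That the trial will report improvement as harm.** This would follow only if the faulty sentence were applied and the bands were not.
- **That a sign convention for change scores is missing.** Such a convention normally belongs in the analysis plan, which is not shown, so its absence is not a finding.

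**Conclusion.** The BI direction is wrong as written. This is an error in an outcome definition, not in arithmetic. If the sentence were applied, the conclusion on daily living would reverse in full; estimates, two-sided p-values, sample size and power would not change. The conclusion rests only on the article's own bands and needs no outside source on the scale.

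The MOCA verb conflicts with the cut-off and with the stated aim of improvement, and merits a wording correction. Reading the pilot changes as gains is an assumption. The rest of the article supports it, but the pilot data are not shown. With that correction, 93 and then 103 per group and power of about 90% remain.

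**What to change.** 1. In the Barthel Index section, replace the direction sentence with: *A higher score indicates better (more independent) living ability.* The bands stay as they are.
2. In the Sample size section, check the sign of the pilot MOCA changes against the pilot data. If they were gains, change *reduce* to *increase*; the figures 3.17 ± 2.12 and 4.40 ± 2.59 stay.

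The cost is one sentence, one word and one look at the data of a 20-case pilot. Design, planned tests, sample size and assessment schedule are untouched. The BI correction should be in place before the results are interpreted.
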